## Abstract

**Background::**

Functional constipation is a disease with a high incidence, which has a bad effect on general health, mental health, and social functioning. However, current treatment is sometimes unsatisfactory. Acupuncture has been proven effective in some randomized controlled trials. Acupressure is a subtype of acupuncture and can be manipulated by the patients at home. But the evidence is limited now. This study aims to provide some strict evidence for the use of self-administered acupressure in the treatment of functional constipation.

**Methods::**

This 2-armed, parallel, nonspecific controlled, randomized trial will be conducted at The Third Affiliated Hospital of Zhejiang Chinese Medical University in Hangzhou. A total of 154 FC patients will be enrolled into the acupoint group and the sham acupoint group with a ratio of 1:1 into this trial and it will consist of a 2-week run-in period, an 8-week intervention period, and an 8-week follow-up period. The treatment will be done by the patients themselves at home twice a day and they should sign in on the WeChat APP every day to make sure they have done the acupressure. The outcome will also be collected in WeChat APP through the diary and questionnaires. For the one who is unable to use the WeChat, the print edition of the diary and questionnaires are provided and the supervision will be done by the short message. The primary outcome will be the proportion of participants whose CSBM≥3 during week 3 to 10. The secondary outcome will be the proportion of participants whose CSBM ≥3 between 2 groups in week 11 to 18, Spontaneous bowel movements, Bristol Stool Form Scale, Straining severity scores, Patient assessment of constipation quality of life, and Medicine use.

**Discussion::**

Acupressure is not an invasive method and can be done by the patient itself at home. We hope this trial will provide credible evidence to the application of self-acupressure for the management of severe chronic functional constipation.

**Trial registration::**

This trial has been registered at the Chinese Clinical Trial Registry (ChiCTR2000038594).

## Introduction

1

Functional constipation (FC) is a disease without an organic etiology and is accompanied by infrequent bowel movements, hard stools, and difficult defecation. It is now believed to be caused by a disorder of gut-brain interaction and the diagnosis of FC, which should rule out irritable bowel syndrome with constipation, opioid-induced constipation, and functional defecation disorders.^[1]^ Severe chronic FC is defined as fewer than 3 complete spontaneous bowel movements (CBSM) per week for more than 3 months.^[2]^ According to a large meta-analysis of 45 population-based surveys, almost 14% of the global population is affected by chronic constipation.^[3]^ There are 1 million visits for chronic constipation in the United States annually.^[4]^ This disease involves large medical costs and has a negative effect on general health, mental health, and social functioning.^[5]^ Moreover, constipation may also increase the risk of cardiovascular diseases, such as venous thromboembolism.^[6]^

Current management of chronic constipation includes lifestyle modification (fiber intake, fluids, and exercise), pharmacology therapies (bulking agents, osmotic laxatives, stimulant laxatives, prokinetics, and secretagogues), biofeedback therapy, and surgery.^[7]^ However, medication for chronic constipation sometimes cannot satisfy patients due to inadequate or temporary relief of the symptoms.^[7]^ Moreover, medication results in some side effects. Biofeedback therapy is effective for rectal evacuation disorders, but it may require multiple clinic visits and is only available in some specialized centers.^[1]^ As monotherapies have limitations and cannot satisfy all the needs of patients, alternative treatments have become increasingly popular.^[8]^

Acupuncture has long been used in the management of constipation in China. It has been proven effective in some randomized controlled trials (RCTs).^[9,10]^ Acupressure is a subtype of acupuncture. It uses fingers, elbows, and hands to press specific acupoints to open up the flow of qi to treat constipation. It has been proven effective in constipation patients with advanced cancer,^[11]^ as well as in pregnant^[12]^ and psychiatric patients.^[13]^ Compared with acupuncture, acupressure can be performed by oneself at home instead of at specific clinics. However, the number of RCTs remains small, and the trials have a high/unclear risk of bias. Thus, we designed an RCT to investigate the safety and efficacy of self-administered acupressure to improve symptoms of FC. Furthermore, we hope that this trial will provide evidence for the integrated use of self-administered acupressure to treat FC.

## Methods/design

2

### Study design

2.1

This study will be a randomized, 2-arm, parallel, sham-controlled trial. This study will be conducted at The Third Affiliated Hospital of Zhejiang Chinese Medical University from July 2021 to July 2023. A total of 154 FC patients will be enrolled into 2 groups (acupoint group and sham acupoint group) at a ratio of 1:1 in this trial, which will consist of a 2-week run-in period, an 8-week intervention period, and an 8-week follow-up period. The Ethics Committee of the Third Affiliated Hospital of Zhejiang Chinese Medical University approved this study (ZSLL-ZN-2021-002-01). The first edition of the protocol, which was registered at the Chinese Clinical Trial Registry (ChiCTR2000038594) on September 30, 2019, was developed as required by the Standard Protocol Items: SPIRIT 2013. The study design is illustrated in a flow chart in Figure 1.

**Figure 1 F1:**
[figure not shown]
Flowchart of the trial.

### Participants and recruitment

2.2

#### Primary process of recruitment

2.2.1

Participants will be recruited from the general population of Hangzhou Zhejiang. We will publicize the trial in multimodal strategies, including WeChat official accounts, newspapers, and recruitment posters at outpatient departments or inpatient wards.

The participants who are interested in the trial will contact us via WeChat or mobile phone. Informed consent must be obtained before the first interview. We will check if the participant meets the Rome IV Criteria and select the participant according to the inclusion and exclusion criteria. After the former procedure, the participant will enter the 2-week run-in period, during which the baseline information of the defecation will be collected, and the registered acupuncturist will teach the participants the location of the point and the details of the acupressure manipulation. The baseline assessment includes CBSMs, spontaneous bowel movements, the Bristol Stool Form Scale (BSFS),^[14,15]^ straining severity scores, and patient assessment of constipation quality of life (PAC-QOL).^[16]^ The study schedule is summarized in Table 1.

**Table 1 T1:** Schedule of recruitment, intervention, and assessments.

	Study period																		
TIMEPOINT	Interview	Baseline		Treatment								Follow-up							
Week		1	2	3	4	5	6	7	8	9	10	11	12	13	14	15	16	17	18
RECRUITMENT	×																		
Informed Consent	×																		
Eligibility Screen	×																		
Demography	×																		
Medical History	×																		
Randomization		×																	
INTERVENTIONS																			
Acupoint self-administered acupressure				×	×	×	×	×	×	×	×								
Sham acupoint self-administered acupressure				×	×	×	×	×	×	×	×								
ASSESSMENT																			
The proportion of participant whose CSBM≥3		×	×	×	×	×	×	×	×	×	×	×	×	×	×	×	×	×	×
SBM		×	×	×	×	×	×	×	×	×	×	×	×	×	×	×	×	×	×
BSFS		×	×	×	×	×	×	×	×	×	×	×	×	×	×	×	×	×	×
Straining severity scores		×	×	×	×	×	×	×	×	×	×	×	×	×	×	×	×	×	×
PAC-QOL				×			×				×				×				×
Medicine usage		×	×	×	×	×	×	×	×	×	×	×	×	×	×	×	×	×	×

#### Diagnostic criteria

2.2.2

The diagnostic criteria will be according to the Rome IV Criteria for FC, which was revised from Rome III by the Rome Foundation in 2016.^[1]^

#### Inclusion criteria

2.2.3

The inclusion criteria are as follows:

(1)Satisfaction of Rome IV Criteria for FC(2)Two or fewer mean weekly Rome IV Criteria for more than 3 months(3)Age between 18 and 65 years(4)No administration of rescue medicine (glycerol or sorbitol anal enema) 48 hours before the trial or any medication for constipation before enrollment for at least 2 weeks(5)No administration of any other therapy for constipation, such as acupuncture, acupressure, or biofeedback therapy, and no participation in any other trial in the previous 3 months.(6)Documented consent to participate in the whole study

#### Exclusion criteria

2.2.4

The exclusion criteria are as follows:

(1)Constipation possibly caused by irritable bowel syndrome, or inflammatory or structural bowel diseases(2)Constipation possibly caused by drugs or endocrine, metabolic, neurologic, or postoperative diseases(3)Presence of tumors, severe cardiovascular, hepatic, renal diseases, or other severe diseases(4)Inability to cooperate because of cognitive dysfunction, aphasia, mental disorders, or other illness(5)Pregnant women, lactating women, or those who plan to get pregnant in the following 3 months(6)Presence of abdominal aortic aneurysm or hepatosplenomegaly(7)Skin lesions at the operating site of the acupoints

### Intervention

2.3

After randomization, the registered acupuncturist will teach the participants the location of the acupoints and the details of the acupressure manipulation in the first 2-week run-in period. The participants will be provided with pictures, text descriptions, and videos about the acupressure manipulation for further study at home. At the end of the second week, the participants will be asked to go to the clinical trial laboratory to be checked by the registered acupuncturist to manipulate the acupressure accurately. Self-acupressure will be performed twice a day during the intervention period, and the patient should sign in on WeChat every day. If the participant is unable to use WeChat, the print edition of the diary and questionnaires will be provided, and the supervision will be performed by short messages. Participants who do not have 3 or more bowel movements can use 100 mL glycerol or 40 to 60 mL sorbitol anal enema with detailed documentation.

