### Randomization and blinding

2.6

The participants will be enrolled in the experimental and control groups at a ratio of 1:1. An independent researcher will generate the randomization sequence using SPSS (SPSS 21.0, SPSS Inc., Chicago, IL). The random numbers will then be placed in opaque envelopes, which will be numbered sequentially and sent to the independent researcher in charge of randomization. The envelopes will be opened sequentially according to the numbers. Then, allocation is determined. The former researcher will unmask the envelopes after interviewing; therefore, the participants and other investigators will be blinded to the allocation. Outcome assessors, data managers, and statisticians will be blinded in this trial and will be separated so that they cannot share information. Furthermore, we will set a standard procedure for communication to ensure treatment blinding. The allocation will be revealed once the trial is completed.

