### Date analysis

2.9

SPSS (version 21.0; SPSS Inc., Chicago, IL) will be used in statistical analyses by an independent statistician. Continuous variables will be presented as mean ± standard deviation, while categorical variables will be represented as percentages and numbers. The Chi-square test will be used to assess categorical variables, such as the characteristic and demographic data. The *t* test or Wilcoxon rank-sum test will be used for within- and inter-group comparisons according to the homogeneity and normality analysis. The date of the participant receiving at least one treatment will be included in the analysis. Missing data will be dealt with using the worst-case scenario method. We set the confidence interval to 95%. All tests are 2-tailed, and *P*-values <.05 will be considered to be significantly different.

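### Participants are allocated two weeks before treatment can start, but the analysis keeps those with at least one treatment, so early losses become post-randomisation exclusions from the primary comparison

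*Protocol article*

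**What the plan says.** Three places in the protocol article fix the time of allocation, and they agree.

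- Section 2.3 (Intervention), which sets this teaching in the run-in weeks: "After randomization, the registered acupuncturist will teach the participants the location of the acupoints and the details of the acupressure manipulation".
- Table 1 ("Schedule of recruitment, intervention, and assessments"), in section 2.2.1: the randomisation mark stands in the week 1 column, the first of two baseline weeks. Eligibility, demography and medical history are marked at the interview.
- Section 2.6 (Randomization and blinding): "The former researcher will unmask the envelopes after interviewing".

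The same two weeks supply the baseline. Section 2.2.1 says that after the eligibility check "the participant will enter the 2-week run-in period, during which the baseline information of the defecation will be collected", and then: "The baseline assessment includes CBSMs, spontaneous bowel movements, the Bristol Stool Form Scale (BSFS"), followed by straining and PAC-QOL.

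Treatment comes later. Section 2.3: "Self-acupressure will be performed twice a day during the intervention period". Table 1 marks acupressure in weeks 3 to 10 only.

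Section 2.9 sets the analysis population: "The date of the participant receiving at least one treatment will be included in the analysis" (the first noun is evidently meant to be data). It also handles missing data by a worst-case method. Section 3 (Discussion) concedes that those who teach the acupressure cannot be blinded, and says that patients will not know their group.

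**The concern.** Randomisation protects a comparison when everyone allocated is counted in the arm to which they were allocated. Here there is a two-week gap between allocation and the first session that can qualify a participant for analysis. A participant who withdraws, stops answering or does not attend the end-of-week-2 check has been randomised but has had no treatment, and so drops out of the denominator.

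The gap is not empty. During it participants are taught arm-specific points, and technique is checked, by an acupuncturist who knows the allocation. Departures could therefore be related to arm, and the trial would have no protection if they were. The worst-case rule applies to missing values of people inside the analysis set, so it does nothing for people outside it. At stake is the primary outcome, the proportion with CSBM of at least 3 in weeks 3 to 10.

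A lesser concern is that the diary baseline (CSBM, SBM, BSFS, straining) and PAC-QOL are recorded after allocation, with the diary kept while participants are learning their allocated points. Section 2.9 plans within-group comparisons, which presumably use that baseline.

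**Working it through.** **1. Order of events.**

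| Step | When | Source |
|---|---|---|
| Consent, eligibility, demography, history | Interview | Table 1 |
| Envelope opened | After interview; week 1 | 2.6; Table 1 |
| Arm-specific teaching | Weeks 1–2 | 2.3 |
| Baseline diary | Weeks 1–2 | 2.2.1; Table 1 |
| Technique check | End of week 2 | 2.3 |
| First PAC-QOL | Week 2 (2.4.2.5) or week 3 (Table 1) | both after allocation |
| First treatment | Week 3 | 2.3; Table 1 |
| Entry to analysis set | First treatment | 2.9 |

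The interval in which a randomised participant can be lost without entering the analysis is therefore weeks 1 and 2.

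**2. The plan's own figure.** Section 2.5 gives 77 per group, 154 in total, after 10% dropout. No response rates are given, so the full calculation cannot be reproduced. The dropout step is consistent with 69 evaluable per arm: 69/(1 − 0.10) = 76.7, rounded up to 77. Ten per cent of 77 is 7.7, so 8 losses is about one arm's whole allowance.

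**3. Size of the exclusion effect (assumed inputs).** Suppose both arms have the same true response rate p among all 77 randomised, and L participants, none of whom would have responded, are lost in weeks 1 to 2 from one arm only. The rate in that arm becomes 77p/(77 − L), while the other arm stays at p. The spurious difference is 77p/(77 − L) − p = pL/(77 − L).

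| Assumed p | L = 4 | L = 8 |
|---|---|---|
| 15% | 0.15 × 4/73 = 0.8 points | 0.15 × 8/69 = 1.7 points |
| 20% | 0.20 × 4/73 = 1.1 points | 0.20 × 8/69 = 2.3 points |
| 30% | 0.30 × 4/73 = 1.6 points | 0.30 × 8/69 = 3.5 points |

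The sign depends on which arm loses people: losses in the acupoint arm favour acupressure, and losses in the sham arm favour sham.

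**4. Other loss patterns.** With 8 lost in one arm and 4 in the other, the spurious difference at p = 20% is 15.4/69 − 15.4/73 = 22.3% − 21.1% = 1.2 points. With 8 lost in each arm it is zero, but both rates read 22.3% instead of 20.0%.

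**5. With all randomised participants analysed.** If the worst-case rule counts a never-starter as a non-responder (the article does not define the rule further), both denominators are 77 and the spurious difference is zero in every row above.

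**The case against.** The strongest reply is that little is likely to happen. Participants are blinded and nobody has started treatment, so there is limited reason for departures to differ by arm. The week-2 check has no stated fail criterion, and the acupuncturist is given no power to exclude. The largest figure above needs about a whole arm's dropout allowance to fall in two weeks, in one arm, among future non-responders. Even then 3.5 points is small beside the difference that 69 per arm could detect with 80% power, roughly 19 to 25 points for assumed control rates of 10 to 40%. All of this stands as an argument about size. It does not answer why the plan should leave the exclusion in place, since the denominator is easily protected. It might also be said that 2.9 does not literally say that others are excluded. But it names no other population, and this is its natural reading.

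A reader might infer four stronger things that the article does not support.

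- *That the run-in fails as a screen.* The article gives it no screening purpose. Eligibility is settled at the interview, and the stated uses of the run-in are baseline collection and teaching.
- *That the late baseline biases the primary outcome.* That outcome is a responder proportion in weeks 3 to 10, with no baseline adjustment stated.
- *That participants are treated during baseline.* Daily pressing is prescribed only for the intervention period. Section 2.3.1 has points chosen partly by how they feel when pressed, so some pressing while learning is plausible, but its extent is unknown. If it worked, it would improve the baseline and shrink apparent change.
- *That the whole baseline is unprotected.* Demography, history and eligibility come before allocation.

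**Conclusion.** The point holds for the analysis set. The article itself fixes allocation before the run-in, treatment from week 3, and analysis conditional on a first treatment, so losses in weeks 1 to 2 are excluded after randomisation from the primary comparison and escape the worst-case rule. Bias arises only if losses are unequal, or differ in kind, between arms. The range of about 0.8 to 3.5 points rests on assumed response rates of 15 to 30% and 4 to 8 non-responders of 77 lost in one arm only. It is an illustration, because the article gives no figures from which the actual bias could be computed. Selective removal by the unblinded teacher is possible in principle but is not something the article describes.

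The timing of the baseline is secondary. It weakens within-group and change-from-baseline results and the baseline comparison of diary measures and PAC-QOL, and does not touch the primary outcome directly.

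**What to change.** **Main change, one sentence in 2.9.** Analyse every randomised participant in the allocated arm, whether or not a session was performed, and apply the stated worst-case rule to those who never start, spelling out what it makes of them for the primary outcome. The total stays at 154. The change remains possible after recruitment has begun, because section 2.6 reveals the allocation only when the trial is completed. The cost is some dilution: if 8 of 77 in each arm never start and count as non-responders, the difference among starters is multiplied by 69/77 = 0.90.

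**Optional, if recruitment allows.** Open the envelope at the existing end-of-week-2 visit, once the baseline diary is complete, and amend 2.3, 2.6 and Table 1. This removes the cause and restores a pre-allocation diary baseline. Its cost is real: participants would have less time to learn their points, which section 2.3.1 requires them to find partly by sensation, before pressing alone at home.

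**If the present order is kept.** State that within-group change from the run-in baseline is descriptive.

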#### Details of the acupressure

2.3.1

In addition to the international standard of the location of the acupoints, the proper acupoints will be selected by the sensation of pressing. The proper acupoints should also be more sensitive than the surrounding areas. The thumb or middle finger can be used to perform acupressure. The force of self-pressing must be sufficiently strong but still within a comfortable range. The participants will be instructed to perform acupressure using circular movements. Each acupoint will be pressed for 1 minute.

#### Experimental group: Acupoint self-administered acupressure group

2.3.2

The 3 acupoints have been selected according to the consensus of acupuncture experts and a previous RCT on acupuncture for chronic constipation.^[17]^ The acupoints are as follows: bilateral Tianshu (ST25), bilateral Fujie (SP14), and bilateral Shangjuxu (ST37).

#### Control group: Sham acupoint self-administered acupressure group

2.3.3

The acupoints are as follows: bilateral sham Tianshu (ST25), bilateral sham Fujie (SP14), and bilateral sham Shangjuxu (ST37). All the sham points are 1 cun outside parallel to the real point.

#### Symptomatic relief medications

2.3.4

Participants who do not have 3 or more bowel movements will be allowed to use 100 mL glycerol or 40 to 60 mL sorbitol anal enema.

### Outcome

2.4

Participants will be required to complete a diary of constipation throughout the trial on WeChat. Most outcomes will be extracted from the diary. Moreover, some questionnaires must be completed. If the participant is unable to use WeChat, the print edition of the diary and questionnaires will be provided.

#### Primary outcome

2.4.1

The primary outcome of this trial is the proportion of participants whose CSBM is ≥3 during weeks 3 to 10 (bowel movements with a sensation of complete evacuation).^[2]^

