##### CSBM in weeks 11–18

2.4.2.2

This signifies comparing the proportion of participants with CSBM ≥3 between the 2 groups in weeks 11 to 18.

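### The CSBM ≥3 responder outcome and its test make no use of the run-in diary, so a participant already at 3 per week counts as a responder without change

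*Protocol article*

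**What the plan says.** Section 2.4.1 (Primary outcome): "The primary outcome of this trial is the proportion of participants whose CSBM is ≥3 during weeks 3 to 10". Section 2.4.2.2 applies the same threshold to follow-up, "comparing the proportion of participants with CSBM ≥3 between the 2 groups in weeks 11 to 18". Neither section mentions a baseline value or a change from one.

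The Introduction defines severe chronic functional constipation as "fewer than 3 complete spontaneous bowel movements (CBSM) per week for more than 3 months". The entry criterion in section 2.2.3 is worded differently: "Two or fewer mean weekly Rome IV Criteria for more than 3 months". What is being counted there is garbled; CSBM is the natural reading, and I assume it here.

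Section 2.2.1 checks eligibility first, and then "the participant will enter the 2-week run-in period, during which the baseline information of the defecation will be collected". Nothing makes the diary a second eligibility check. Table 1 places randomisation in week 1. Section 2.3 has the acupuncturist teach the technique after randomisation, during the run-in.

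Section 2.9 names a chi-square test for categorical variables, with baseline characteristics as its example. It mentions no covariate adjustment.

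**The concern.** The trial collects two weeks of each participant's own CSBM counts just before treatment, and the stated responder outcomes then set them aside. Eligibility rests on recalled history. Someone who recalls two or fewer per week may record three or more in the run-in, stay there, and be counted as a responder.

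Two things are at stake. First, a reader of the responder percentage cannot tell who moved across the threshold from who was already above it. Second, run-in CSBM is likely to be one of the strongest predictors of later CSBM, and an unadjusted comparison in a 154-person trial gives up the precision it would bring.

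**Working it through.** **The plan's own figure.** Section 2.5 gives 154 in total, 77 per group, with 10% dropout, 80% power and alpha 0.05. The dropout step is consistent: 69 / (1 − 0.10) = 76.7, rounded up to 77. The 69 evaluable per arm cannot be reproduced because no response rates are given. It would fit, for example, a sham rate of 10% with a difference of about 0.19, or 20% with about 0.22.

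**Can someone be at 3 in the diary without change?** Assume Poisson weekly counts with a constant true rate λ. A run-in mean ≥3 needs at least 6 CSBM in two weeks. At λ = 2 this is 1 − P(Poisson(4) ≤ 5) = 1 − 0.785 = 21.5%. An 8-week mean ≥3 needs at least 24 in eight weeks. At λ = 2 this is 1 − P(Poisson(16) ≤ 23) = 3.7%.

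| True CSBM/week | Run-in mean ≥3 | ≥3 in a given week | 8-week mean ≥3 |
|---|---|---|---|
| 1 | 1.7% | 8% | 0.0% |
| 1.5 | 8.4% | 19% | 0.1% |
| 2 | 21.5% | 32% | 3.7% |
| 2.5 | 38.4% | 46% | 21% |

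**Over a mixed population, no treatment effect (simulation).** Every input is an assumption:
- true rates gamma with shape 2 and mean 1.5–2.5 before selection;
- entry on a recalled 12-week mean ≤2;
- recall error SD 0–0.5 and drift between periods SD 0–0.3, both on the log scale.

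Results:
- About 5–15% of entrants already average ≥3 in the run-in. A second set of assumptions (mean 0.8–2.0, Poisson or overdispersed counts, history of 2 or 12 weeks) gives about 2–14%.
- Response without any effect is 1–11% if the 8-week mean must be ≥3 (0.2–9.8% in the second set). It is 4–19% if four of eight weeks suffice, and 11–21% week by week.
- With recall error and drift, 38–54% of the no-effect responders on the 8-week mean were already at ≥3 in the run-in.

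**Would a required rise help?** Power at n = 69 per arm is Φ{[|p₁ − p₂| − 1.96√(2p̄(1 − p̄)/n)] / √([p₁(1 − p₁) + p₂(1 − p₂)]/n)}. For an assumed gain of 1 CSBM per week on the 8-week mean, sham versus acupoint:

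| ≥3 only | Power | ≥3 and rise ≥1 | Power |
|---|---|---|---|
| 9.8% v 25.7% | 0.690 | 5.3% v 18.5% | 0.671 |
| 2.3% v 14.6% | 0.743 | 1.4% v 11.7% | 0.690 |
| 5.1% v 20.5% | 0.779 | 2.0% v 14.1% | 0.748 |

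Further simulations gave 0.51 to 0.45, 0.61 to 0.52, 0.77 to 0.67, 0.61 to 0.57 and 0.62 to 0.54. Power fell in every pair, by about 2 to 10 points, because the rule discards true responders along with noise.

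**Does adjustment help?** Chi-square versus logistic regression adjusted for run-in mean CSBM, 69 per arm, true gain 0.8–1.0 per week: 51% v 60%, 61% v 64%, 77% v 77%. Another run in noisier settings gave 0.61 v 0.71 and 0.62 v 0.72. There the adjusted test rejected 6–7% of the time under no effect, so part of that gain reflects a slightly liberal test. In low-noise settings the ordinary logistic fit is unstable: at a 1% sham rate only 0.01 × 69 = 0.7 sham responders are expected.

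**The case against.** The strongest reply is that the threshold is deliberate. Section 2.5 says the primary outcome is the same as in the earlier acupuncture study used for planning. The trial is randomised against sham, so background responders are expected equally in both arms. Table 1 records the same measure in weeks 1 and 2, so the run-in proportion can be reported beside the outcome. The choice of model is commonly left to an analysis plan that is not shown, and section 2.9 does not expressly assign the chi-square test to the primary outcome. All of this stands. It is why the threshold should stay and why this is an improvement, not the repair of an error.

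A reader might also infer more than the document supports:
- *That response is the exact complement of the entry condition.* It is the complement of the Introduction's disease definition. Entry is two or fewer, which on the CSBM reading leaves a gap of 1 per week between recalled history and response. The gap does not apply to the diary.
- *That noise or regression to the mean biases the result.* It does not bias the comparison between arms.
- *That the trial is underpowered because of this.* For a fixed 20-point difference, power at 69 per arm is about 92%, 84% and 78% at sham rates of 5%, 10% and 15%. These values lie on both sides of 80%. The planning rates are not stated and may already include background responders.
- *That the primary outcome should require a rise.* The power figures above go the other way.

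**Conclusion.** The point holds as a modest one. The responder outcomes for weeks 3–10 and 11–18 make no use of the run-in diary, and the only test named for categorical data is unadjusted. Under assumed CSBM variability, about 5–15% of entrants could already be at ≥3 in the run-in and count as responders without change; a second set of assumptions puts the lower end nearer 2%. The larger no-effect response rates arise only where a few weeks or single weeks count. They reflect how the eight weekly counts are combined, which section 2.4.1 does not say and which is a separate matter.

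The consequence is a blurred meaning of responder and unused baseline information. In the simulations, adjustment left power unchanged in one setting and raised it by 3 to 10 points in the others. Part of the largest gains comes from the slightly liberal test noted above. No figure here comes from trial data, and none shows a loss against the planned 80%.

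**What to change.** Keep CSBM ≥3 as the responder rule for both periods, so that the outcome still matches the earlier acupuncture study. Compare arms with a logistic regression of response on arm and run-in mean CSBM instead of an unadjusted chi-square test. State in advance that a penalised (Firth) fit will be used if sham responders are sparse, preferably with a penalised likelihood-ratio test, since Wald tests behave poorly with few events.

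Add one prespecified sensitivity analysis that defines a responder as ≥3 CSBM per week and at least 1 per week above the participant's run-in mean. It shows how many responders improved on their own diary. It should not become the primary outcome.

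One condition applies. Table 1 randomises in week 1 and the technique is taught during the run-in, so diary days after practice begins could already carry an effect, and adjusting for them would remove part of it. The protocol should state that the covariate is recorded before any acupressure is practised, and reconcile the run-in timetable with that.

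The cost is wording, slightly more analysis work, and an adjusted odds ratio to report. The diary is already collected, and the sample size and visits do not change.
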